### Outcome {12}

#### Primary outcome measure

The main outcome is the incidence of VF following aortic opening within 30 min during extracorporeal circulation.

#### Secondary outcome measures

The secondary outcomes are the energy and frequency of electrical defibrillation, pacemaker use, anesthesia time, CPB time, aortic occlusion time, and operation time in the two groups.

The other data are heart rate, mean arterial pressure (MAP), and central venous pressure (CVP) at the time of anesthesia induction (T1), surgery (T2), cardiopulmonary bypass (T3), aortic occlusion (T4), aortic opening (T5), after opening for 10 (T6), 20 (T7), and 30 min (T8), at cessation of cardiopulmonary bypass (T9), and completion of surgery (T10). Blood gas analysis results at T1, T5, T9, and T10 are also recorded and compared (Fig. 1).

**Fig. 1 Fig1:**
[figure not shown]
Flowchart

### Participant timeline {13}

**Table Taba:** 

*Event*	*Timepoint*					
	**Preoperative**		**Intraoperative**			
	***T*****0**	***T1T2T3***	***T4***	***T5***	***T6T7T8***	***T9T10***
**Recruitment**						
Eligibility screening	**X**					
Informed consent	**X**					
Random allocation	**X**					
**Intervention**						
Esmolol			**X**			
Amiodarone			**X**			
**Data collation**						
Base variable	**X**	**X**	**X**	**X**	**X**	**X**
Primary outcomes					**X**	
Secondary outcomes				**X**	**X**	**X**
Other data	**X**	**X**	**X**	**X**	**X**	**X**
**Assesment**						
Incidence of ventricular fibrillation					**X**	

*T0* pre-entry, *T1 *anesthesia induction, *T2 *surgery begins, *T3 *cardiopulmonary bypass, *T4 *aortic occlusion, *T5 *aortic opening, *T6 *after opening for 10 min, *T7 *20 min, *T8 * 30 min, *T9 *at cessation of cardiopulmonary bypass, *T10 *completion of surgery

### Determination of sample size

We determined the required sample size based on the prevalence of VF as the primary outcome. A previous retrospective study found that the incidences of VF are 39% [11] and 23% [12] in patients treated with amiodarone or esmolol, respectively, prior to aortic opening. A sample size of 127 patients per group is appropriate to finish the trial to detect a difference with 80% power and a 5% type I error rate. Given the potential for patient dropouts, a sample of 130 patients per group is required.

## Assignment of interventions: allocation

### Implementation {16b}

Following randomization, information will be placed in envelopes that are sealed. A nurse anesthetist from the study group will open the envelopes on the day of surgery in the order of assignment, and esmolol and amiodarone will be provided based on the grouping. An anesthesiologist who is not informed of the grouping will then conduct the study. The outcome evaluation will be carried out by a trained anesthesiologist, and the data analysis will be done by a different anesthesiologist. They are not both aware of the group assignment. At the preoperative visit, the patient signs an informed consent form, which is then given to the principle investigator.

### Enrolling {16c}

After seeing the patient, the anesthesiologist is in charge of recruiting participants.

### Double-blind randomization and allocation concealment

The 260 patients will be divided randomly into the intervention group and control group in a ratio of 1:1 using a computer-generated sequence.

### Blinding {17a}

The anesthesiologist will not be informed of the patient assignments, which are recorded and sealed in sequentially numbered opaque envelopes. Nurse anesthetists can give sealed envelopes and tell them to prepare the items for the experiment based on group allocations; there are no differences in the look of the two sets of envelopes. The group assignment will be withheld from all patients and anesthesiologists. Following anesthesia induction, the anesthesiologist may perform the various surgeries in accordance with the coded number. Another anesthesiologist will document intraoperative data and follow up on the patient’s discharge. Finally, the data will be analyzed by a professional statistician.

### Unblinding {17b}

A blinding committee will be convened, which consisted of experts to oversee and guide the blinding process. At the end of the trial, after the completion of the locking library, in order to carry out the analysis, the first level of blinding, so as to know each subject as group A or B, but do not know the specific group A and B group operation. On the basis of primary blinding, statistical analysis is performed to clarify the difference between group A and group B. Secondary blinding will be then performed to know the operation group information of each subject, to clarify whether it is the intervention group or the control group, and to further analyze the results of the clinical trial. The blinding results will be recorded in a blinding form and confirmed and signed under the supervision of a blinding committee. Under the direction of a blinding committee, the outcomes of the blinding will be documented in a blinding form and verified and signed.

The data will not be released until the final statistical analysis has been completed.

## Data collection and management

### Plans for assessment and collection of outcomes {18a}

Dedicated staff will record all data and complete a case report form for each patient. Relevant demographic characteristics and the patients’ past medical histories, including age, height, weight, and diagnosis, will be collected at the time of patient inclusion. Intraoperative data including heart rate, MAP, and CVP will be recorded at the induction of anesthesia (T1), start of surgery (T2), start of extracorporeal circulation (T3), aortic block (T4), aortic opening (T5), after opening for 10 (T6), 20 min (T7), and 30 min (T8), at cessation of extracorporeal circulation (T9), and at the end of surgery (T10), and blood gas analysis will be recorded at T1, T5, T9, and T10.

### Plans to promote participant retention and complete follow-up {18b}

Not applicable. We believe that the focus of our experiment is on various markers during the perioperative phase. On the day of the procedure, the patient will be monitored until the patient is discharged from the PACU. We shall employ the same data collecting and statistical forms for all experimental data.

### Data management {19}

The Principal Investigator is accountable for the data’s correctness, completeness, readability, and timeliness. Investigators will keep correct medical history report forms and background material for research participants in their medical records.

### Confidentiality {27}

All researchers are professional clinical or scientific experts and will strictly abide by the regulations on patient information protection and ethical safety. Personal information that has been recorded is handled with the utmost confidentiality and processed and stored in line with data protection legislation. Except for parties directly involved in the subject’s care and organizations to whom the subject has given express agreement, no patient-identifiable information will be transmitted to anyone else.

### Statistical analysis

Statistical analysis will be performed using SPSS software, version 26.0 for Windows (SPSS, Inc., Chicago, IL, USA). Continuous variables will be described as mean (standard deviation) or median (25% and 75% percentile) and will be analyzed using independent *t*-tests or Mann–Whitney *U*-tests, respectively. Categorical variables will be described as a frequency or percentage and will be analyzed by *χ*^2^ tests. Prior to statistical analysis, each continuous variable will be analyzed to determine if it is normally distributed. If the assumption of a normal distribution is violated, the appropriate transformation will be used.

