### Subgroup analyses {20b}

At this moment, subgroup analyses have not been taken into account. The variables employed in the minimization algorithm will be subjected to subgroup analyses, but only for the main result, if necessary.

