### The treatment of non-adherence and missing data {20c}

Analyses will be performed with intention-to-treat: all participants will be analyzed according to the block to which they are randomly assigned. In addition, the trial includes the intraoperative administration of two drugs and the monitoring of intraoperative-related data. The amount of data lost is expected to be minimal.

The researchers will make every effort to collect all follow-up data on all participants, and almost all data will be collected in the perioperative period. Therefore, it is expected that missing data will be minimal. Subjects with missing co-primary outcome data will not be included in the primary analysis in the first place. Each randomized group’s result data is summarized separately. By comparing baseline characteristics of subjects with missing and imputed values, potential bias owing to missing data will be examined. Missing predictors can be identified using the number of missing values. The missing predictors will subsequently be included as covariates in the main analytical model via a sensitivity analysis. Various multiple interpolation algorithms can also be used if necessary.

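### The chi-square test of the primary outcome is valid but forgoes precision from age and diagnosis, and two other sections presuppose a minimization algorithm and a covariate model that the article does not contain

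*Protocol article*

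**What the plan says.** All references are to the protocol article.

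- **Outcome.** Primary outcome measure: "The main outcome is the incidence of VF following aortic opening within 30 min during extracorporeal circulation". This is a yes/no outcome per patient.
- **Test.** Statistical analysis: "Categorical variables will be described as a frequency or percentage and will be analyzed by" χ² tests. The only other tests named are t-tests and Mann–Whitney tests, for continuous variables. No regression model and no covariate appear there.
- **Allocation.** Double-blind randomization and allocation concealment: patients are divided "in a ratio of 1:1 using a computer-generated sequence". Implementation {16b}: "Following randomization, information will be placed in envelopes that are sealed". Neither section names a stratification or minimization factor.
- **Subgroups.** Subgroup analyses {20b} first says that subgroups have not been considered, then adds: "The variables employed in the minimization algorithm will be subjected to subgroup analyses", for the main result and only if needed. The variables are not named.
- **Missing data.** The treatment of non-adherence and missing data {20c}: as a sensitivity analysis, predictors of missingness are to be "included as covariates in the main analytical model".
- **Baseline data.** Plans for assessment and collection of outcomes {18a} lists age, height, weight and diagnosis among the data recorded at inclusion.
- **Sample size.** Determination of sample size: "the incidences of VF are 39% [11] and 23% [12] in patients treated with amiodarone or esmolol", giving 127 per group "to detect a difference with 80% power and a 5% type I error rate", raised to 130 for dropout.

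**The concern.** There are two separate issues.

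The first is efficiency. The trial pools heart valve and aortic surgery and has little power to spare. Age and diagnosis are recorded before treatment, so they can be used in the primary comparison at no extra burden. If they predict VF, an unadjusted test leaves precision on the table.

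The second is coherence. Minimization makes each assignment depend on the characteristics of patients already enrolled, so it is a different method from drawing on a computer-generated 1:1 sequence. The article mentions both. Which was used matters, because factors used to balance the arms belong in the analysis. Likewise, the missing-data sensitivity analysis needs a model that accepts covariates, and the only primary test described accepts none. If this is left open, the model and its covariates would have to be chosen later, possibly with results in view.

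**Working it through.** **1. Does the sample size match the unadjusted test?** Inputs from Determination of sample size: 39% and 23%, 80% power, 5% type I error. Two-sided testing is assumed, since sidedness is not stated.

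- Unpooled variance: n = (1.960 + 0.842)² × (0.39×0.61 + 0.23×0.77) / 0.16² = 7.849 × 0.4150 / 0.0256 = 127.2 per group, which rounds to the stated 127.
- Pooled variance: n = 130 per group.
- Power of the pooled test: 79.1% at 127 and 80.0% at 130 per group.

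The stated figure is reproduced, and the unadjusted two-proportion comparison is its basis.

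**2. What would adjustment add?** The article gives no prognostic strength for any baseline variable, so every gain below rests on an assumption.

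*Approximation.* If covariates remove a share R² of outcome variance, the effective size is n/(1 − R²). Power at 127 per group, and the n per group needed for 80%:

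| R² (assumed) | Power at 127 | n for 80% |
|---|---|---|
| 0 | 79.1% | 130 |
| 0.05 | 81.1% | 124 |
| 0.10 | 83.2% | 117 |
| 0.15 | 85.2% | 111 |
| 0.20 | 87.3% | 104 |

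*Simulation A.* 130 per arm, one binary covariate (40% prevalence) and one normal covariate, marginal risks 39% and 23%, 3,000 trials per setting:

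| Combined AUC (assumed) | Chi-square | Adjusted logistic | Difference (points) |
|---|---|---|---|
| 0.50 | 80.4% | 79.9% | −0.5 |
| 0.64 | 79.3% | 81.2% | +1.9 |
| 0.72 | 80.6% | 84.6% | +4.0 |
| 0.76 | 80.2% | 87.2% | +7.0 |

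The simulation standard error of each figure is about √(0.8×0.2/3000) = 0.7 points, so −0.5 is no material loss.

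*Simulation B.* 127 per group, one normal covariate, 4,000 trials per setting:

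| Odds ratio per SD (assumed) | Chi-square | Adjusted logistic |
|---|---|---|
| 1.0 | 79.2% | 78.9% |
| 1.5 | 79.1% | 79.3% |
| 2.0 | 79.2% | 82.1% |
| 2.5 | 79.0% | 84.3% |

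*Simulation C.* A further run at 130 per arm gave 82% against 81% with weak covariates, 85% against 81% with stronger ones, and no loss with uninformative ones.

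**3. Is the chi-square valid?** In the null runs of simulation B (31% in both arms, allocation not balanced on the covariate), its rejection rate was 4.4% to 5.8%. The adjusted test gave 4.3% to 5.7%. The simulation standard error is √(0.05×0.95/4000) = 0.3 points. Both are close to the nominal 5%.

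**4. What if the arms were in fact balanced on a prognostic covariate?** With allocation forced into very tight balance, a limiting case of minimization, the chi-square rejection rate under the null was 5.0%, 4.6%, 4.0% and 3.3% at odds ratios of 1.0, 1.5, 2.0 and 2.5 per SD. Ignoring the balancing factors makes the test conservative.

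**5. Do the sections agree?**

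- *Allocation against subgroups:* the allocation section describes a computer-generated sequence, while the subgroup section takes its variables from a minimization algorithm. One of the two needs correcting.
- *Statistical analysis against missing data:* a χ² test compares two proportions and has no place for a covariate. The step that adds predictors to a main model cannot be applied to it as written.

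**The case against.** The strongest reply is that the primary test is correct. Under a simple 1:1 sequence the chi-square is valid, and the trial was sized on it. The gain from adjustment is hypothetical: one covariate with an odds ratio of 1.5 per SD adds nothing visible, and the larger gains need predictors that the article does not show to exist. Model details may also sit in an analysis plan that is not shown. All of this stands. It limits the first issue to forgone precision, but it does not reconcile the sections compared in step 5.

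A reader might infer more than the article supports:

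- *That chance imbalance is left uncorrected.* With an assumed 40:60 surgery mix, the SD of the between-arm difference is √(2×0.4×0.6/130) = 6.1 points, so a difference above 10 points has about a 10% chance. The type I error already allows for this. If VF risk differed by 15 points between surgery types (assumed), a 10-point imbalance would shift the risk difference by 0.10 × 15 = 1.5 points, against a standard error of about √(2×0.31×0.69/130) = 5.7 points.
- *That baseline data go unused.* The missing-data section uses them to look for bias. They are absent only from the primary comparison.
- *That planned subgroup analyses are lost.* They are conditional and declared not currently planned.
- *That sealed envelopes rule out minimization.* The envelopes are filled after randomization, and the participant timeline puts allocation at T0 for each patient, so envelopes alone do not exclude patient-by-patient assignment. The conflict is with the computer-generated sequence.
- *That unrecognized minimization would inflate false positives.* Step 4 shows the opposite direction.

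**Conclusion.** The point holds as an improvement and a repair of inconsistent text. It is not a flaw in the validity of the primary test. Adjusting for type of surgery and age is worth roughly 1 to 7 points of power in the simulations with moderately to strongly prognostic covariates. It is worth close to nothing with a weak one, and costs nothing material if they are uninformative. The variance approximation reaches 87.3 − 79.1 = 8.2 points at R² = 0.20. These sizes depend entirely on assumed prognostic strength.

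The two conflicts do not depend on any assumption. The minimization reference contradicts the described sequence, and the covariate sensitivity analysis cannot be run on the only primary test described. An analysis plan that is not shown might define the model, but it could not make both descriptions of the allocation true.

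**What to change.** Before unblinding:

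1. **Primary analysis.** Use a logistic regression of VF on arm, adjusted for type of surgery (valve or aortic, derived from the recorded diagnosis) and age. Report the standardized risk difference with its 95% confidence interval, and state in advance which result decides superiority. Keep the chi-square as supportive. This also supplies the model that the missing-data section needs.
2. **Allocation.** State the method actually used. If it was the simple sequence, delete the minimization reference from Subgroup analyses {20b}. If it was minimization, correct the randomization section, name the factors, and adjust for them in the primary model.

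No interaction test is required.

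The cost is analysis wording plus the ethics approval that the article requires for protocol changes. No new patients or data are needed. SPSS can fit the model. The standardized risk difference needs one further step: averaging predicted risks under each arm, with a delta-method or bootstrap interval. With completion expected in March 2024, the change should be dated and filed before the group codes are opened.

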### Subgroup analyses {20b}

At this moment, subgroup analyses have not been taken into account. The variables employed in the minimization algorithm will be subjected to subgroup analyses, but only for the main result, if necessary.

### The treatment of non-adherence and missing data {20c}

Analyses will be performed with intention-to-treat: all participants will be analyzed according to the block to which they are randomly assigned. In addition, the trial includes the intraoperative administration of two drugs and the monitoring of intraoperative-related data. The amount of data lost is expected to be minimal.

The researchers will make every effort to collect all follow-up data on all participants, and almost all data will be collected in the perioperative period. Therefore, it is expected that missing data will be minimal. Subjects with missing co-primary outcome data will not be included in the primary analysis in the first place. Each randomized group’s result data is summarized separately. By comparing baseline characteristics of subjects with missing and imputed values, potential bias owing to missing data will be examined. Missing predictors can be identified using the number of missing values. The missing predictors will subsequently be included as covariates in the main analytical model via a sensitivity analysis. Various multiple interpolation algorithms can also be used if necessary.

### Interim analyses {21b}

Regular meetings will be held to evaluate and correct the trial as necessary. However, at this trial, interim analyses are not planned.

## Oversight and monitoring

### Experimental steering and data monitoring committee {5d}

A team of researchers will manage or supervise this single-center study. To monitor study progress and track study status, the primary investigator will hold monthly phase meetings (overall study and study design), as well as a study steering committee meeting to maintain ongoing contact between investigators and discuss study progress. A core team of the principal investigator, an experienced cardiac surgeon, a clinical pharmacist, and a data statistician are in charge of the study’s conduct, adherence to the study protocol, patient safety, and the review of new information related to the study questions. The trial will not require a data monitoring committee because the risk of adverse outcomes is low. Of course, any major adverse events, problems, or injuries will be reported to and documented by the CMU Scientific Ethics Committee.

### Reported adverse events {22}

Any negative experience a participant has while taking part in the study is referred to as an adverse event (AE), regardless of whether it is thought to be related to the intervention. From the moment of drug application to day 3 following surgery, AEs will be carefully observed in this trial. The investigator will keep track of all AE information, including type, diagnosis date, duration, care, and outcomes. The Principal Investigator will be informed of any serious adverse events and will judge the severity and causality of these events. All authorized entities associated with the study will be recorded and reported to the Ethics Committee as part of the annual report.

The study will be stopped if there is a serious adverse event (SAE).SAEs include death, disability, and severe allergic reactions that seriously affect the health of the patient.

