## Background

Advancements in surgical methods, aids, and cardiopulmonary bypass (CPB) techniques have increased the indications for open heart surgery. However, cardiac surgery and CPB are still associated with potentially fatal consequences, such as bleeding, infection, and arrhythmias. Arrhythmias are the most severe complication, and ventricular fibrillation (VF) is the most severe secondary arrhythmia [1, 2], with reperfusion VF occurring in 70–96% of cases of CPB [3, 4]. Pathophysiologically, VF is associated with aortic opening-induced myocardial ischemia and reperfusion injury, together with the ensuing inflammatory reactions, oxidative stress, and electrical instability [5]. Electrical defibrillation has been the gold standard treatment for VF after aortic opening; however, electrical defibrillation may aggravate myocardial damage and lead to cardiac dysfunction, as well as recurrent and fatal arrhythmias [6]. Preventive measures are therefore needed to reduce the risk of VF after aortic opening during open heart surgery and improve patient outcomes.

Antiarrhythmic medications have been shown to be effective for treating VF following aortic opening during cardiac surgery, with amiodarone and esmolol chosen as the representative medicines for clinical use. As a class III antiarrhythmic medication, the main electrophysiological mechanism of amiodarone involves lengthening the action potential and effective refractory period of cardiac tissue, hence preventing return-excitation. Amiodarone also slows the conduction rate by inhibiting the fast influx of sodium ions into the conduction fibers of the atria and myocardium. However, its ability to prevent VF is inconsistent [7, 8]. Esmolol is a selective beta 1 blocker with a very short half-life, which has been shown to accelerate spontaneous cardiac recovery following aortic opening and decrease the incidence of reperfusion VF [9].

Their pharmacological properties and past research suggest that both amiodarone and esmolol can successfully prevent and cure reperfusion VF following CPB. We hypothesized that esmolol would be more effective in this regard, and accordingly designed a clinical trial to compare the efficacies of amiodarone and esmolol for preventing reperfusion VF during open heart surgery.

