## Interventions

### General anesthesia

All patients will receive conventional general anesthesia as follows: induction with midazolam 0.05 mg/kg, etomidate 0.3 mg/kg, sufentanil 0.5 µg/kg, and cis-atracurium 0.2 mg/kg. The anesthesia machine is connected after tracheal intubation, the tidal volume is set at 6–8 mL/kg, and the respiratory rate is 12 breaths/min. The intraoperative end-tidal CO_2_ pressure is maintained at 35–45 mmHg by adjusting the respiratory parameters, and the bispectral index (BIS) is maintained at 40–60. Anesthesia will be maintained with continuous pumping of propofol 4–8 mg/kg/h, with scheduled replenishment of sufentanil and cis-atracurium. Heparin 300 IU/kg is given intravenously at the beginning of the operation, and esmolol is administered to patients in the intervention group after the activated clotting time reached > 480 s. Esmolol will be administered by a single-dose bolus (usually 500 μg/kg) followed by a continuous infusion (between 100 and 300 μg/kg/min or titrated in order to maintain low heart rates). Patients in the control group will receive extracorporeal circulation and the surgical operation is completed, and 300 mg of amiodarone is then administered 10 min before aortic opening. Drug infusion is stopped 10 min after opening the aorta in both groups. If electrical defibrillation is required after aortic opening, defibrillation is initially performed using 20 J, and if this is ineffective twice, defibrillation is repeated using 30 J. If defibrillation is unsuccessful after 3 attempts, a second dose of study medication will be administered on the basis of prior randomization. Patients in the control group will receive an additional 150 mg of amiodarone. At the end of the procedure, the patient will be returned to the cardiac surgery unit under ventilatory ball-assisted ventilation.

A five-lead electrocardiogram, ambulatory blood pressure, oxygen saturation, end-expiratory CO_2_ pressure, BIS, and nasopharyngeal temperature will be monitored throughout the procedure and blood gas analysis will be performed at regular intervals.

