## Discussion

Continuous improvements in surgical techniques and the prudent use of anti-inflammatory drugs have greatly reduced the incidence of complications such as bleeding and infection after direct cardiac surgery, causing reperfusion VF after CPB aortic opening to become a more prominent and fatal complication. The mechanism of reperfusion VF is complex and it is currently thought to be caused by a combination of factors resulting in decreased and increased non-conductivity of myocardial cells during the non-reperfusion period. Reperfusion VF induces a severe stress response characterized by increased sympathetic activity, myocardial oxygen consumption, myocardial ischemia, and myocardial injury.

Intraoperative hypothermia and cold myocardial protective fluid are currently used to reduce the occurrence of reperfusion VF, but it remains a potentially fatal complication after myocardial reperfusion.

Antiarrhythmic drugs are commonly used by cardiac anesthesiologists to prevent and treat VF. Previous research showed that amiodarone not only improved the metabolic efficiency of the heart after ischemia reperfusion, but also reduced the transmural dispersion of cardiac repolarization, which is strongly linked to the development of reperfusion VF [13, 14]. In contrast, esmolol has been proposed to enhance the overall balance of myocardial oxygen supply and demand during resuscitation, potentially by minimizing the delay in cardiomyocyte depolarization produced by receptor excitation, thereby lowering the heart’s oxygen demand [15]. However, high-quality human study data are lacking.

The results of the current study may be useful in clinical settings, to lessen myocardial damage and thereby enhance survival. We reduced the impact of differences between individual anesthesiologists and cardiac surgeons by analyzing surgical procedures performed by the same surgical team, with all anesthesia provided by a single anesthesiologist.

The drug doses and administration techniques used in this study are chosen based on prior studies; however, the doses of amiodarone and esmolol used may not be sufficient to achieve therapeutic concentrations, taking into account the increased circulating volume of the CPB circuit.

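### As written, a single serious adverse event of any cause stops the whole 260-patient trial

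*Protocol article*

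**What the plan says.** The stopping rule is one sentence in Reported adverse events {22}: "The study will be stopped if there is a serious adverse event (SAE". The next sentence defines the trigger: "SAEs include death, disability, and severe allergic reactions that seriously affect the health of the patient". No threshold, arm comparison, pause or review step is attached.

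The preceding paragraph of that section defines an adverse event "regardless of whether it is thought to be related to the intervention" and observes patients from first study drug until day 3 after the operation. It says that the principal investigator "will judge the severity and causality of these events", and it provides for an annual report to the Ethics Committee.

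Three other places bear on the reading:

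- General anesthesia: "Drug infusion is stopped 10 min after opening the aorta in both groups".
- Experimental steering and data monitoring committee {5d}: "A core team of the principal investigator, an experienced cardiac surgeon, a clinical pharmacist, and a data statistician are in charge" of conduct and patient safety. This section also decides against a data monitoring committee, on the ground that adverse outcomes are unlikely.
- Interim analyses {21b}: none are planned, although regular meetings may correct the trial.

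**The concern.** What is stopped is the study, the trigger is one event, and nothing qualifies it. The investigator's causality judgement is collected, but the stopping sentence does not use it.

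The population makes this more than a formality. The Background says that "cardiac surgery and CPB are still associated with potentially fatal consequences, such as bleeding, infection, and arrhythmias", and the Discussion says of reperfusion ventricular fibrillation, the primary outcome, that "it remains a potentially fatal complication after myocardial reperfusion". A death or disabling event within three days of such surgery, with no link to esmolol or amiodarone, is foreseeable.

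Following the rule could end the trial far short of its planned size for a reason that says nothing about either drug. Ignoring it would be a departure from the published protocol that the final report must explain.

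**Working it through.** **Inputs from the protocol article.** Total 260, allocated 1:1 (Double-blind randomization and allocation concealment). Ventricular fibrillation in 39% on amiodarone and 23% on esmolol, 80% power, 5% type I error, 127 per group raised to 130 for dropout (Determination of sample size). Sidedness is not stated; two-sided is used here.

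**Input assumed.** The per-patient risk *p* of at least one SAE between first study drug and day 3, all causes and both arms together. The document gives no figure, so *p* is varied from 0.1% to 2%.

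**Step 1: the plan's own figure.** With the unpooled normal approximation,

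n = (1.960 + 0.842)² × (0.39×0.61 + 0.23×0.77) / 0.16² = 7.849 × 0.415 / 0.0256 ≈ 127.2 per group,

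which agrees with the stated 127. The pooled version gives 130. Pooled power at 130 per group is 80.0%, so the planned power is confirmed.

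**Step 2: chance that the literal rule halts the trial.** P(at least one SAE in 260) = 1 − (1 − p)^260. The median patient at the first SAE is ln(0.5)/ln(1 − p), rounded up.

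**Step 3: power at the median halt.** With n = N/2 per arm and pooled proportion 0.31,

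power = Φ{[0.16√n − 1.960 × √(2×0.31×0.69)] / √0.415} = Φ{[0.16√n − 1.282] / 0.644}.

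For example, N = 69 gives n = 34.5, and Φ[(0.940 − 1.282)/0.644] = Φ(−0.53) ≈ 0.30.

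| Assumed SAE risk | Chance of halt before 260 finish | Median patient at first SAE | Power there |
|---|---|---|---|
| 0.1% | 22.9% | 693 (beyond 260) | – |
| 0.25% | 47.8% | 277 (beyond 260) | – |
| 0.5% | 72.8% | 139 | 53% |
| 1% | 92.7% | 69 | 30% |
| 2% | 99.5% | 35 | 17% |

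**Step 4: break-even rates.**

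- Even chance of a halt: 1 − 0.5^(1/260) = 0.27%.
- 95% chance of a halt: 1 − 0.05^(1/260) = 1.15%.
- 80% chance of reaching 260: 1 − 0.8^(1/260) = 0.086%.

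**Step 5: does any other text narrow the rule?**

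- *Stopping drug in the affected patient.* The infusion ends 10 minutes after aortic opening in both arms, so for nearly all of the observation window no study drug is left to stop.
- *Stopping only for related events.* Causality is judged, but the stopping sentence does not refer to that judgement.
- *Another body or boundary.* There is no data monitoring committee and no interim analysis. The core team is given responsibility for safety but no role in this rule.

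**The case against.** The best case against is that the authors cannot have meant an automatic halt. Judging causality, reporting annually to the Ethics Committee and holding monthly meetings all presuppose a trial that continues after an SAE. The article's English is loose in places, so the sentence may mean ending that patient's participation, which would suit non-fatal events throughout the window. The clause about relatedness belongs to the definition of an adverse event for recording, in the preceding paragraph, and is conventional there; the stopping sentence is merely silent on cause. The size depends on an assumed rate, with results from 23% to 99.5%, and the article itself calls the risk low. Finally, recruitment began in November 2019, the article appeared in November 2023 and completion was expected in March 2024, so most of the exposure had passed.

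Much of this stands. A narrower intention is plausible, the true SAE rate is unknown, and an amendment at this stage would cover few patients. None of it corrects the sentence. Silence on cause, joined to a definition in which any death counts, yields a rule that an unrelated death triggers. Causality review and annual reporting show that the section conflicts with itself. A fuller protocol might add conditions, but the published sentence is already categorical. The late stage moves part of the value of a correction from conduct to reporting.

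**Conclusion.** The concern holds: the stopping sentence is wrong as written and should be fixed. Confidence is high about what the sentence says and lower about its practical effect.

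If the rule is applied literally, an all-cause SAE risk above about 0.27% per patient makes a halt more likely than not, and about 1.15% makes it 95% likely. At 0.25% or below the trial more likely than not completes. A halt at the median patient for risks of 0.5% to 2% would leave power between about 53% and 17%.

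These figures assume independent patients with a common risk, an immediate halt at the first event, equal arms at that point, and the protocol's own event rates. They do not show that a halt was probable in this trial, because the document gives no SAE rate.

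**What to change.** Replace the stopping sentence with a rule at two levels:

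- **Patient:** an SAE stops study drug in the affected patient if it is still being given.
- **Trial:** every SAE triggers prompt review by the existing core team and the Ethics Committee, covering causality and cumulative SAEs by arm. A halt is their documented decision, on criteria agreed with the Ethics Committee, and never follows automatically from one event.

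The cost is a wording amendment approved by the route in Plans for communicating important protocol modification {25}. Both bodies already exist, and no extra patients or data are needed. Because the trial was near its expected end when the article appeared, the final report should also say whether any SAE occurred and, if recruitment continued, on what basis.
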